### Sample size calculation

In our study a sample size of 25 in each group (or 50 in total) will have a 80% power to detect a difference in mean percentages of fibrosis of at least 25% using a two group t-test with a 0.05 two-sided significance level (alpha). In this calculation we used the following assumptions: we expect the control group (no MSC’s) to have a mean percentage of fibrosis of 18% at 6 months [38-43]. We assume that both groups show equal variability in measured fibrosis and that the common standard deviation is 5% [40]. A mean percentage of 14% in MSC group (25% less fibrosis) is considered a clinically relevant difference. We anticipate that 70% of included patients will have valid measurements (withdrawal included). We therefore plan to include 70 patients in total, 35 in the MSC group and 35 in the control group.

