## Methods and design

### Objectives and endpoints

The primary end point of the current study is the level of fibrosis, as determined by quantitative Sirius Red (SR) scoring of biopsies of MSC treated and untreated groups at 6 months compared to 4 weeks post transplantation. Other endpoints include: composite endpoint efficacy failure (Biopsy Proven Acute Rejection (BPAR), graft loss) at 6 months; renal function measured by eGFR (MDRD formula and iohexol clearance) and proteinuria at 6 months; cytomegalovirus (CMV), BK infection (viremia, disease and -syndrome) and other opportunistic infections; adverse events; the presence of DSA and other phenotypical and functional aspects of the donor specific immune response; to compare the progression of “subclinical” cardiovascular disease in the different treatment groups by assessing echocardiography.

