
One of the important issues in the MSC-based clinical trials is defining endpoints, as this is the measure of trial failure or success. However, this is very challenging in patients after solid organ transplantation, where an increased risk for infections and malignancies already exists and where there is a lack of validated surrogate markers of disease. The therapeutic aim of MSC-based trials in renal transplant recipients is to induce immune suppression and repair of damaged tissue but without the risk of inducing tumours, infections, or unwanted tissue development, and obviously without increasing allograft rejection rates and diminishing allograft survival. Therefore both safety and efficacy measures have to be addressed. Efficacy markers in our trial include laboratory studies to determine possible development of donor-specific immunosuppression and histopathologic evaluation of renal tissue to evaluate both inflammation and fibrosis before and after the treatment. The primary endpoint in our study is the comparison of fibrosis by quantitative SR scoring of MSC treated and untreated groups at 6 months compared to 4 weeks post-transplant. Once established, interstitial fibrosis and arteriolar hyalinosis lead to progressive glomerulosclerosis over the subsequent years. In earlier studies nephrotoxicity, implicated in late ongoing injury, has been shown to be almost universal at 10 years, even in grafts with excellent early histologic findings. By 10 years, severe chronic allograft nephropathy was present in 58.4% of patients, with sclerosis in 37.3% of glomeruli. Tubulointerstitial and glomerular damage, once established, was irreversible, resulting in declining renal function and graft failure [38,53-56]. Functional studies underestimate the extent of allograft disease as supported by longitudinal studies of protocol renal biopsies showing histologic features of IF/TA in well-functioning grafts [38,39,56-58]. Therefore, early histologic detection of IF/TA has been suggested to be helpful in predicting the risk for subsequent loss of function and time to graft failure and to estimate the efficacy of therapeutic measures. Semiquantitative grading systems such as Banff scores have a wide inter-observer variation that makes comparison across centers inaccurate. In contrast, computerized image analysis of fractional interstitial fibrosis of SR-stained biopsies has been shown to be a valid and reproducible method to measure the degree of fibrosis [40,41,43,59,60]. SR dye is specific for collagen types I and III, which represent respectively 80 and 20% of total collagen synthesized by fibroblasts and thereby important components of renal matrix. Quantification of renal interstitial volume assessed by SR nonpolarized technology has been validated and correlated significantly with GFR as measured by iothalamate clearance in cases of established chronic allograft nephropathy [59]. In addition, in 2011 morphometric and visual evaluation of fibrosis by various techniques was compared and Collagen III, SR unpolarized had strongest correlations, greatest dynamic range and the best correlation with estimated GFR [61].

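### The stated 80% power belongs to a comparison of 6-month fibrosis levels; it is not shown to apply to the primary endpoint, which is defined relative to the 4-week biopsy

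*Protocol article*

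**What the plan says.** The Objectives and endpoints section gives the primary endpoint as the level of fibrosis "determined by quantitative Sirius Red (SR) scoring of biopsies of MSC treated and untreated groups at 6 months compared to 4 weeks post transplantation". The Methods/design part of the abstract says the same in substance, and the Discussion repeats it as the "comparison of fibrosis by quantitative SR scoring of MSC treated and untreated groups at 6 months compared to 4 weeks post-transplant". All three places bring in the 4-week biopsy.

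The Sample size calculation section does not. It states that 25 patients in each group "will have a 80% power to detect a difference in mean percentages of fibrosis of at least 25% using a two group t-test", at a two-sided 0.05 level. The control group is expected to "have a mean percentage of fibrosis of 18% at 6 months". The MSC group is put at 14%, with a common SD of 5% in measured fibrosis. The section gives no 4-week mean, expected change, SD of change or correlation between the two biopsies.

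The section on fibrosis scoring says that the 4-week biopsy is a study biopsy taken to see the histology before infusion. No section says how its Sirius Red value enters the primary comparison: as a change, a ratio or a covariate.

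**The concern.** The endpoint and the power statement describe different quantities. The SD of a 6-month level is not the SD of a change from week 4. Which is larger depends on how strongly two separate biopsies from the same graft are correlated, and the article does not address this. If the endpoint is analysed in its most natural reading, as a change from week 4, the only power figure in the article does not describe that analysis.

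The open wording also matters in itself. The trial is open label and small, and the article supports more than one reading of its primary comparison. Unless one is fixed beforehand, the choice could be made after the data are seen.

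**Working it through.** **Inputs from the Sample size calculation section:** control mean 18%, MSC mean 14%, so a difference of 4 points; SD 5; 25 per arm; two-sided alpha 0.05; two-group t-test.

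**Inputs not in the documents, so assumed:** the correlation r between the 4-week and 6-month values, and the 4-week SD, s. The protocol's common SD is common to the two groups; it is not stated to hold at both time points.

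**Step 1: reproduce the stated figure.** Standardised difference = 4/5 = 0.8. With 25 per arm, power is 79.1% (noncentral t) or 80.7% (normal approximation). The stated 80% is therefore correct for the 6-month level. It was computed with 4 points, although 4/18 = 22% and not 25%. A literal 25% (4.5 points) would give 87.7%.

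**Step 2: unadjusted change score.** Under randomisation the expected difference in change equals the difference in 6-month means, so the 4 points carry over. Only the SD alters:

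SD of change = √(5² + s² − 2·r·5·s) = √(25 + s² − 10rs)

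With s = 5 this becomes 5·√(2(1 − r)). Power at 25 per arm and the number needed per arm for 80%, both by noncentral t:

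| r | SD of change | Power | n per arm for 80% |
|---|---|---|---|
| 0 | 7.07 | 50% | about 50 |
| 0.2 | 6.32 | 59% | 41 |
| 0.3 | 5.92 | 65% | 36 |
| 0.4 | 5.48 | 72% | 31 |
| 0.5 | 5.00 | 79% | 26 |
| 0.7 | 3.87 | 95% | 16 |

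**Step 3: dependence on the 4-week SD.** The SD of change exceeds 5 when s² − 10rs > 0, that is when r < s/10. For s = 5 the threshold is r = 0.5. For s = 3 it is r = 0.3: there the SD of change is √(25 + 9 − 9) = 5.00 and power is 79%, against 65% at the same r with s = 5.

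**Step 4: ANCOVA of the 6-month value on the 4-week value.** Residual SD = 5·√(1 − r²), which does not depend on s. Power at 25 per arm:

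| r | Residual SD | Power |
|---|---|---|
| 0 | 5.00 | 79% |
| 0.3 | 4.77 | 83% |
| 0.5 | 4.33 | 89% |
| 0.7 | 3.57 | 97% |

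All figures in steps 2 and 4 take 25 per arm as patients with both values.

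**The case against.** The best defence is that an unadjusted t-test on the final value is a common and conservative way to size a comparison that will be adjusted for baseline. Step 4 bears this out: ANCOVA has essentially the stated power at r = 0 and more at any higher correlation. The model may also be set out in an analysis plan that is not shown, and a condensed article need not give it. This stands as far as it goes: the planned number of patients need not be wrong. It does not remove the mismatch, because the article gives both the endpoint and the powered comparison and does not connect them.

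Three stronger readings are tempting, and the documents do not support them.

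- A reader might infer that the true power is only 59–65%. That needs an unadjusted change score, r of 0.2 to 0.3 and a 4-week SD of 5, none of which is in the article. Nor is it a floor (50% at r = 0), and power exceeds plan when r is above 0.5. Low correlation between separate needle cores is plausible but undocumented.
- A reader might infer that the protocol prescribes a 6-month-only t-test and discards the 4-week biopsy. The t-test appears in a sample size section, which does not name the primary analysis.
- A reader might infer that 4 points means abolishing most of the later progression. That depends on a 4-week fibrosis level the article does not give. The Background also reports that areas of fibrosis disappeared after MSCs in the phase 1 study, so the envisaged effect is not limited to slowing progression.

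**Conclusion.** The mismatch is certain: the primary endpoint is defined relative to week 4, and the 80% is the power of a comparison of 6-month levels. The stated power is therefore not shown to apply to the primary endpoint.

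The documents fix neither the size nor the direction of any error. For an unadjusted change score with an assumed 4-week SD of 5, power runs from 50% (r = 0) to 95% (r = 0.7) and falls below plan only if r is under 0.5, or under 0.3 if the 4-week SD is 3. For a baseline-adjusted analysis it stays at about the planned level or above. The conclusion is that the endpoint and its power need to be reconciled, not that the trial is shown to be underpowered.

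**What to change.** Name a single primary analysis: the between-arm comparison of the 6-month Sirius Red percentage by ANCOVA, with the 4-week Sirius Red percentage as covariate. Word the endpoint to match in the abstract, the Objectives and endpoints section and the Discussion.

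Restate the power for that analysis and give the assumed correlation: about 79% at r = 0, 83% at 0.3 and 89% at 0.5, with 25 evaluable patients per arm. If a change score is preferred instead, state the assumed SD of change, or r and the 4-week SD, and recompute the sample size from it.

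The cost is wording in the protocol and analysis plan. With ANCOVA no patients or biopsies are added, because the 4-week and 6-month biopsies are already scheduled in both arms.

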### Risk-benefit assessment

The high prevalence of nephrotoxicity suggests that CNI are unsuitable as long-term immunosuppressive agents for kidney transplantation and MSCs might offer an alternative treatment modality with the aim to inhibit fibrosis and to prolong allograft survival. In previous studies in transplant recipients, MSC therapy was shown to be feasible and no major serious side effects have been reported so far. One of the risks of CNI withdrawal is an increased risk of acute allograft rejection. Therefore renal function and trough levels of the immune suppressive drugs will be monitored frequently. In addition, the type of induction therapy (alemtuzumab) and the timing of CNI withdrawal (>6 weeks) are chosen to minimize risks for allograft rejection. We think that early clinical results, which suggest beneficial effect from MSC administration for patients after renal transplantation and the expected limited possibility on adverse side effects justify participation in this study.

## Discussion

The great potential for MSC therapy to become a new tool after renal transplantation as immune suppressive and reparative treatment is strengthened by positive preclinical results, the ease of isolation and expansion of MSCs and encouraging preliminary trials. Since current immunosuppressive drugs cannot be withheld from patients receiving MSC treatment after renal transplantation, it is of importance that an optimal concurrent immunosuppressive regimen is chosen with minimal side effects. The objective of the current study is to implement MSC treatment in combination with everolimus to facilitate CNI withdrawal with the aim to preserve renal function and structure.

Since the early 1980, the standard approach to immunosuppression in transplant recipients has involved the use of CNI such as cyclosporine (CsA) and tacrolimus. Most centres nowadays use a regimen of basiliximab, mycophenolate mofetil (MMF), and corticosteroids in combination with low-dose tacrolimus, based on the Symphony trial [44]. However, immune suppressive drug treatment is becoming more and more individualized. CNI nephrotoxicity may account for the paradox that the reduction or abolition of early episodes of acute rejection has not resulted in commensurate improvements in the long-term outcome [1,45]. The damage by CNI is not reversed by mild-to-moderate reductions in the dose of these agents [45]. However, the optimal treatment strategy to reduce or eliminate CNI therapy at an early time point after transplantation, without compromising efficacy, is unclear. In this perspective MSCs might facilitate CNI withdrawal. In our protocol, we have chosen for the combination of MSCs with everolimus, prednisolone and alemtuzumab. The combination of an mTOR inhibitor and MSCs might be a potential promising strategy since there is experimental evidence that this combination is tolerogenic [2,9,29] and capable of increasing regulatory immune cells [29]. Of importance, complete avoidance and replacement of a CNI by everolimus in de novo transplant recipients is not justified, since this strategy previously resulted in unacceptable high acute rejection rates even with induction therapy [46]. Both the Caesar and the Symphony study showed that reduced CNI-dosing, as opposed to full dose CNI early after transplantation, are equally efficacious in preventing acute rejection but only marginally improved renal function parameters [44,47]. The CONVERT and the ASCERTAIN study were initiated to replace CNIs by an mTOR inhibitor at a late time-point i.e., 3,2 and 5,6 years respectively, after transplantation [48,49]. This strategy proved to be safe but again only minor improvements in renal function parameters were found and if so, predominantly in patients with still preserved renal function. Contrastingly, in the Zeus study, renal allograft recipients were converted from CNI to everolimus at 4–5 months after transplantation to triple drug regimen with mycophenolate and steroids and reported significantly better renal function up to 3 years after CNI-elimination [50,51]. In our study, CNI will be withdrawn at an earlier time point, namely at 6 weeks after transplantation. To decrease the risk for acute rejections, MSCs will be infused at the time of CNI withdrawal. In addition, alemtuzumab will be used as induction treatment. This induction treatment has been shown to be superior to traditional antibodies in preventing acute rejection. A recent study demonstrated that alemtuzumab-based induction therapy followed by reduced CNI and mycophenolate exposure and steroid avoidance reduced the risk of biopsy-proven acute rejection compared with standard basiliximab in a broad range of patients receiving a kidney transplant [52].

One of the important issues in the MSC-based clinical trials is defining endpoints, as this is the measure of trial failure or success. However, this is very challenging in patients after solid organ transplantation, where an increased risk for infections and malignancies already exists and where there is a lack of validated surrogate markers of disease. The therapeutic aim of MSC-based trials in renal transplant recipients is to induce immune suppression and repair of damaged tissue but without the risk of inducing tumours, infections, or unwanted tissue development, and obviously without increasing allograft rejection rates and diminishing allograft survival. Therefore both safety and efficacy measures have to be addressed. Efficacy markers in our trial include laboratory studies to determine possible development of donor-specific immunosuppression and histopathologic evaluation of renal tissue to evaluate both inflammation and fibrosis before and after the treatment. The primary endpoint in our study is the comparison of fibrosis by quantitative SR scoring of MSC treated and untreated groups at 6 months compared to 4 weeks post-transplant. Once established, interstitial fibrosis and arteriolar hyalinosis lead to progressive glomerulosclerosis over the subsequent years. In earlier studies nephrotoxicity, implicated in late ongoing injury, has been shown to be almost universal at 10 years, even in grafts with excellent early histologic findings. By 10 years, severe chronic allograft nephropathy was present in 58.4% of patients, with sclerosis in 37.3% of glomeruli. Tubulointerstitial and glomerular damage, once established, was irreversible, resulting in declining renal function and graft failure [38,53-56]. Functional studies underestimate the extent of allograft disease as supported by longitudinal studies of protocol renal biopsies showing histologic features of IF/TA in well-functioning grafts [38,39,56-58]. Therefore, early histologic detection of IF/TA has been suggested to be helpful in predicting the risk for subsequent loss of function and time to graft failure and to estimate the efficacy of therapeutic measures. Semiquantitative grading systems such as Banff scores have a wide inter-observer variation that makes comparison across centers inaccurate. In contrast, computerized image analysis of fractional interstitial fibrosis of SR-stained biopsies has been shown to be a valid and reproducible method to measure the degree of fibrosis [40,41,43,59,60]. SR dye is specific for collagen types I and III, which represent respectively 80 and 20% of total collagen synthesized by fibroblasts and thereby important components of renal matrix. Quantification of renal interstitial volume assessed by SR nonpolarized technology has been validated and correlated significantly with GFR as measured by iothalamate clearance in cases of established chronic allograft nephropathy [59]. In addition, in 2011 morphometric and visual evaluation of fibrosis by various techniques was compared and Collagen III, SR unpolarized had strongest correlations, greatest dynamic range and the best correlation with estimated GFR [61].

As secondary endpoints safety measures will be included. An important safety issue includes direct toxicity related to the infusions. Although, to date, no toxicity has been observed during intravenous MSC infusion [11], a possible side-effect of MSC transfusion could be a transfusion reaction (e.g. allergic reaction, fever and hypotension). Another possible side effect could be an increased risk of infection; therefore all donors are thoroughly screened before BM aspiration. In addition, one cannot rule out that a renal transplant recipient receiving MSCs might have a decrease of renal function. In addition, the change in immune suppressive regimen might increase the incidence of acute rejection.

Other potential risks which should be considered when using MSCs for clinical applications include risk for malignancies and opportunistic infections. So far, in clinical trials using MSCs no malignancies have been reported. However most trials have a short follow up and we are still awaiting reports on long-term effects [20,62,63]. Moreover, in many trials patients with a poor prognosis are included where MSC-related side effects might be obscured. In addition, due to the concomitant use of immunosuppressive medications, patients who received a renal transplant are already at enhanced risk of malignancies.

The risk of over immunosuppression, which may lead to opportunistic infections, has been studied in a few reports and will be closely monitored in our trial as well. In a study by Tan et al. on patients undergoing renal transplantation [32], the use of autologous MSCs instead of anti-IL-2 receptor antibody induction therapy resulted in decreased opportunistic infections (including CMV infections). However, CMV donor recipient status was negative in 151 of 154 patients, which might have caused the low incidence of CMV infections in their population. In our previous trial, 3 out of 6 renal recipients developed opportunistic infections [34] and also MSC co-infusion after haematopoietic stem cell transplantation (HSCT) caused a higher 1-year incidence of (particularly fungal) infections [64]. It is clear that frequent and accurate monitoring of infectious complications and also monitoring of the level of immune suppression remains essential.

A number of factors may adversely affect renal structure and function, including ongoing alloimmune injury by cellular and immune reactions. It is therefore of major importance that the immune status is accurately measured in our trial population. Our current protocol will measure DSA at several time points and will encompass a robust immune monitoring strategy, developed by the ONE study consortium which includes procedures for whole blood leukocyte subset profiling by flow cytometry [36]. Our hypothesis is that MSCs induce immune suppression by decreasing the amount of effector cells and increasing the number of regulatory cells. In our previous trial, we have shown that patients receiving MSCs demonstrated a profound reduction in proliferation of PBMC 12 weeks after MSC infusion upon stimulation with donor PBMCs, but there were no consistent changes in immune profiles. In the pilot study by Perico et al. MSC treatment allowed increased numbers of T regs in the peripheral blood and control of memory CD8^+^T cell function [30]. In both studies the amount of included patients was small and it is therefore difficult to draw firm conclusions. In addition, both studies were set up as safety and feasibility studies. In the current trial we anticipate that we can make meaningful comparisons of leukocyte subset profiling in MSC treated and untreated groups.

Cardiovascular disease exerts a high burden in terms of morbidity and mortality in renal recipients. The annual risk of a cardiovascular event is up to 50-fold higher for a renal recipient compared to the general population [65-67] and over a third of all deaths following kidney transplantation are caused by cardiovascular disease [68,69]. Several studies nowadays focus on the proposed cardio protective effects of everolimus in transplant recipients. In heart transplantation everolimus was significantly more efficacious than mycophenolate mofetil in preventing cardiac allograft vasculopathy (CAV) as measured by intravascular ultrasound (IVUS) among heart-transplant recipients after 1 year [70]. Interestingly, this process might be regulated by T regs, which are expanded after treatment of an mTOR inhibitor [71]. However, mTor inhibitors are also capable to increase the frequency of antigen-specific CD8^+^T cells that differentiated into the memory lineage, thus adequate immune monitoring is of major importance [72]. As MSCs have also been proposed to exert reparative properties in cardiovascular disease, the combination of MSCs and everolimus might be an opportunity to reduce the toll of cardiovascular disease following kidney transplantation.

Taken together, we hypothesize that infusion of MSCs enables CNI withdrawal and provides a novel treatment option for renal recipients with a profound effect on the fibrosis reaction and less side effects than existing immunosuppressive therapies. A positive outcome from MSCs in terms of safety and preservation of renal function and structure would implicate a major advancement for renal transplant recipients.

